### Intervention fidelity

Three exercise supervisors will deliver the exercise protocol in a uniform. At random time points, an independent assessor will observe classes and monitor content consistency using a checklist on explicit areas of the exercise protocol. The principal investigator will check the exercise protocol log daily and the independent assessor will review it at random intervals to check that the intervention is delivered as intended.

### Outcome measures

All outcomes are measured pre- (within one week before the start date of the intervention) and post-intervention (within one week after the intervention) (Table 1).

**Table 1 Tab1:** Outcome variables and measuring instruments/procedures

Outcome variable	Measuring instrument/procedure
Anthropometry: Height, weight, body circumferences (waist, hip, mid-arm, mid-thigh)	∙ISAK guidelines. ∙Stadiometer, electronic weighing scale and measuring tape (SECA, Germany)
Body fat %	∙Seven site skin fold measures by ISAK and ACSM guidelines. ∙Harpenden skin fold caliper.
Total and regional body composition	∙Dual energy X- ray absorptiometry (DXA) full body scan. Hologic Discovery W, DXA system.
Cardiovascular endurance/Fitness	∙6 min walk test (6MWT). ∙Queens College/McArdle Step test. ∙Exercise Electrocardiogram (ECG).
Muscle strength	∙ACSM guidelines. ∙One repetition maximum (1RM) testing with machine and free weights (Precor, USA).
Blood pressure	OMRON digital blood pressure monitor (Japan).
Heart rate	Polar heart rate monitors.
Biochemical parameters: Glycemic control (HbA1c FBS, Fasting insulin), lipid level, liver enzymes, HsCRP.	Venous blood samples with overnight fast tested in tertiary care independent laboratory.
Quality of life	SF-36 quality-of-life outcomes questionnaire. Self-administered.
Liking and wanting for different types of food	Computer-based behavioral procedure Leeds Food Preference Questionnaire (LFPQ).Self-administered.

### Primary outcome

#### Change in glycemic control

Primary outcome will be absolute change in glycosylated hemoglobin (HbA1c) levels. HbA1c is the accepted parameter to monitor long-term glycemic control (normal values are 4–6.5%) [32]. Additionally, fasting blood sugar levels (FBS) and fasting insulin (FI) levels will be measured to further assess and compare change in insulin resistance status. A venous blood sample will be collected after an overnight fast by a trained medical officer/investigator and transported to a standard tertiary care laboratory for analysis. Laboratory technicians are blinded to the study participants.

### Secondary outcomes

#### Change in percentage body fat (%BF)

Total body fat percentage will be measured via dual energy X-ray absorptiometry (DXA) full body scan [33], a gold standard method for the assessment of body composition. Additional details on regional body fat will be provided. The DXA scan is completed in a standard tertiary care laboratory by a trained technician who is blinded to the study participants. Body composition will also be assessed using seven skin fold thickness measures (triceps, chest, sub scapular, axillary, mid-thigh, abdominal and suprailiac skin folds) [31] with a Harpenden skin fold caliper by the trained principal investigator. All measurements will be taken in the morning between 0900 and 1000 am by the same investigator to maintain consistency and inter-rater reliability. The ISAK (International Society for the Advancement of Kinanthropometry) methodology and American College of Sports Medicine Guidelines will be used [34].

Skinfold thickness, body circumferences, and DXA will enable a detailed appraisal of total and regional adiposity. The addition of waist circumference and skinfold thickness measures to DXA values will improve data on central adiposity [33].

### Lipid profile, liver profile and chronic inflammatory status

Absolute change in plasma lipid profile, total cholesterol (TC), triglycerides (TG), high-density lipoproteins (HDLC), low-density lipoproteins (LDLC) will indicate change in metabolic and cardiovascular risk of participants [35].Change in highly sensitive serum C-reactive protein (hs-CRP) will be measured to identify the chronic inflammatory status, a predictor of future cardiovascular risk [36].Serum Aspartate aminotransferase/Alanine aminotransferase (AST/ALT) levels will be measured to assess liver cell damage consistent with metabolic derangement in metabolic syndrome and T2DM [37].

### Anthropometry and cardiovascular/fitness parameters

Anthropometry:

*Measurements* will be taken in the morning between 0900 and 1000 am adhering to ISAK guidelines by the trained principal investigator who is a qualified medical practitioner. Height will be measured while the participant is barefoot to the nearest 0.1 cm using a portable stadiometer (Seca 213, Germany). Weight will be measured (wearing light clothing without shoes) using an electronic weighing scale (Seca 813, Germany) and recorded to the nearest 0.1 kg. Body Mass Index (BMI) will be calculated using the standard calculation (weight/height ^2^ kgm^− 2^). *Waist, hip, mid-arm, mid-thigh circumferences* will be measured using a non-elastic measuring tape (Seca 201, Germany) to the nearest 0.1 cm. A mean value will be recorded after three consecutive measurements [31].Cardiovascular endurance and electrocardiographic measures:Exercise ECG will be undertaken at a tertiary care hospital electrocardiographic laboratory under the supervision of a consultant cardiologist and trained staff using the Bruce protocol. Exercise ECG results will provide profile electrocardiographic changes in addition to blood pressure and heart rate changes to progressive exercise.YMCA 3-Minute Step Test will be used to measure heart rate changes with acute progression of exercise [31].The 6-min walk test (6MWT) will be used to measure endurance and the walkability of participants [31].Resting and exercise heart rate will be monitored by heart rate monitors (Polar). Systolic and diastolic blood pressure will be measured using standard methods by trained research assistants using an Omron HEM-7130 electronic sphygmomanometer.Muscular strength: One Repetition Maximum (1RM) will be assessed in all major muscle groups [31].

### Quality of life (QoL)

Change of Quality of Life will be assessed using the SF-36 quality-of-life outcomes questionnaire [38] previously validated in Sri Lanka.

### Liking and wanting of food

Change in preference for a particular type of food (high fat: sweet, high fat: savory, low fat: sweet, low fat savory) will be assessed using the computer-based Leeds Food Preference Questionnaire (LFPQ) [39]. This questionnaire will be customized to the Sri Lankan population by adding Sri Lankan foods to different food categories asked in the questions. The participant will initially be trained to use the computer program by the investigator before being self-administered.

### Qualitative study

The primary outcome of the qualitative study is to identify barriers and facilitators experienced during the prescribed exercise programs using in-depth interviews (IDIs). This will be carried out after the last exercise session of the individual program by the principal investigator and a trained assistant. Face-to-face interviews will be conducted with privacy maintained using a set of pre-determined semi-structured open-ended questions regarding; the stage of behavioral change, knowledge of exercise, individual’s beliefs, perceived ability, limitations/barriers and facilitators experienced during the prescribed exercise programs.

During interviews, written notes will be taken and responses from participants will be audio recorded, including emotional responses. The number of interviews will determined by data saturation which will be revealed during concurrent analysis.

To the best of our knowledge, no studies have been conducted to date where the effectiveness of a RCT has been assessed via the qualitative experience of participants. This component will allow a triangulation approach to incorporate quantitative and qualitative data at the stage of results interpretation.

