**Methods:**

The Sri Lanka Diabetes Aerobic and Resistance Training (SL-DART) Study will be comprised of 2 components. Component 1 is a 12-week randomized controlled trial (RCT) to compare the effects of a supervised progressive resistance exercise program (RT) and aerobic exercise program (AT) with standard treatment/control (CN). Sedentary Sri Lankan adults with T2DM (aged 35–65 years) and with no contraindications to exercise will be randomized into one of 3 groups (AT, RT, CN). Exercise sessions will be conducted 2 days/week for 3 months. Baseline and post-intervention biochemical (glycemic control, lipid and liver profiles, inflammatory markers), anthropometric (height, weight, body circumferences), body composition, physical fitness, food preference (liking and wanting food) and quality of life parameters will be measured and compared between groups. Component 2 will be a qualitative study conducted immediately post-intervention via in-depth interviews to assess the barriers and facilitators for adherence to each exercise program.

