Sri Lanka is also experiencing a socio-economic or nutrition transition, a change from a more active agricultural lifestyle to a more sedentary lifestyle due to industrialization and urbanization and resultant overweight and obesity [6]. Historically, structured recreational exercise has not been a part of the culture in Sri Lanka [11] and it is uncommon to see recreational exercise groups, gymnasia and professionally trained staff. Poor food choices are also contributing to less than desirable health outcomes. For example, only 3–5% of Sri Lankan adults consume the recommended 5 portions of fruits and vegetables per day and diets are characterized by higher portions of rice and less protein (mainly by rice and pulses), almost half that of US adults [12]. Prevention and management of an estimated 1–1.5 million people with pre-diabetes and diabetes is causing an escalating burden to the Sri Lankan economy and society. There is a need to develop effective management strategies to prevent a worsening of the problem.

Exercise is known to improve blood glucose, lipid profiles, blood pressure [13] and visceral adiposity [14], key goals of diabetes management, with food intake and quality of life also considered as important factors. Combined aerobic exercise training (AT) and resistance exercise training (RT) interventions have been widely utilized in white Caucasians populations [15]with benefits also reported for either exercise modality when used individually [16, 17]. It has been suggested that South Asians could benefit more from RT due to their relatively higher adiposity and lower lean body mass compared to Caucasians [18]. Currently, no Sri Lankan studies have documented and very few South Asian studies have compared the effects of AT plus RT on people with T2DM. Secondly, low compliance and adherence is a common drawback in exercise interventions with information on the qualitative factors associated with non-adherence to exercise often overlooked [19]. Finally, relatively few South Asian studies have addressed food intake and the effects of AT and RT on food preference [20].

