### Aims of the study

The primary aim of the Sri Lanka Diabetes Aerobic and Resistance Training (SL-DART) Study is to investigate the effect of two exercise modalities in Sri Lankan adults (aged 35–65 years) diagnosed with T2DM. A 12-week randomized controlled trial (RCT) will compare AT, RT and usual care on the primary outcome measure, glycemic control (HbA1c). Secondary outcome measures include percentage body fat, blood lipid and liver profiles, inflammatory markers, muscle strength, cardiovascular endurance, blood pressure, quality of life attributes and food preferences. A secondary aim is the qualitative assessment of barriers/facilitators to compliance and adherence to different modes of exercise via in-depth interviews.

To the best of our knowledge, a study of this nature has not been conducted in Sri Lanka or in other parts of South Asia. In a culturally diverse setting like Sri Lanka, the development of a feasible exercise intervention for T2DM would therefore be very novel. The experiences of SL-DART Study will enable the development of a culturally acceptable clinical exercise physiology service to people with T2DM.

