## Methods

### Study design

Pilot studyComponent 1: A 12-week RCT will study the effects of a supervised RT and AT program on behavioral, anthropometric, physical fitness, appetite and biochemical parameters in sedentary Sri Lankan adults with T2DM (aged 35–65 years) with no contraindications to exercise. Outcomes will be compared between exercise programs and a control group who receive standard care.Component 2: A qualitative study will be undertaken immediately after the intervention to assess the barriers and facilitators for adherence to each program (refer to Figs. 1 and 2).

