### Sample size

Ninety (*n* = 90) participants will be recruited from a roll-in method and allocated to RT group (*n* = 30), AT group (*n* = 30), or CN group (*n* = 30). The sample size was calculated considering the expected change of glycosylated hemoglobin (HbA1c) (primary outcome) of the participants. HbA1c is the main parameter to check long-term glycemic control [14]. Previous studies have reported that structured AT or RT had statistically and clinically significant reduction of absolute HbA1c by about 0.6% [21, 22]. Sample size was calculated to have 80% power to detect a moderate 0.65-SD difference in HbA1c, with an alpha/α value of 0.05. Additional participants will be recruited until the required number is achieved (*n* = 38) per group to account for the estimated drop-out rate of 15–25%.

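### Barrier interviews are timed after the last session, so on the natural reading AT and RT participants who stop early have no interview point

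*Protocol article*

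**What the plan says.** The protocol article gives the interview time in three places.

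- Abstract, Methods: "Component 2 will be a qualitative study conducted immediately post-intervention via in-depth interviews to assess the barriers and facilitators for adherence to each exercise program".
- Study design: "A qualitative study will be undertaken immediately after the intervention to assess the barriers and facilitators for adherence to each program".
- Qualitative study: "This will be carried out after the last exercise session of the individual program by the principal investigator and a trained assistant".

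The purpose is set out under Aims of the study: "A secondary aim is the qualitative assessment of barriers/facilitators to compliance and adherence to different modes of exercise via in-depth interviews". The Background explains why the component was added: low compliance is common in exercise trials, with "information on the qualitative factors associated with non-adherence to exercise often overlooked".

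The Sample size section plans 30 per group and raises this to 38 to cover an "estimated drop-out rate of 15–25" per cent. The Qualitative study section specifies face-to-face interviews and leaves their number to data saturation. The article describes no interview at withdrawal and no contact with people who have left.

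**The concern.** A component created to learn why people do not keep to an exercise programme is scheduled at a point that those who abandon it would not normally reach. They are likely to know most about the barriers that end participation.

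The Abstract and the Discussion say that the qualitative and quantitative results will be triangulated to design an exercise intervention for Sri Lankans with type 2 diabetes and to inform policy makers. If the people who stopped are thinly represented or absent, the themes may understate the barriers that matter for uptake outside a supervised trial. That direction of bias is plausible, but the documents do not demonstrate it.

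**Working it through.** **1. The three statements of timing.** The abstract and the Study design section tie the interviews to the end of the intervention. The Qualitative study section ties them to the last session of the individual's programme. Taken alone, the last wording could mean the last session that a person happened to attend. Read with the other two, the natural meaning is the end of the 12-week programme. No passage names withdrawal as an occasion for an interview.

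**2. Reproducing the plan's recruitment figure.** Inputs from Sample size: 30 per group, drop-out *d* of 15–25%, 38 recruited per group. Formula: recruited = 30 / (1 − *d*), rounded up.

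| *d* | 30 / (1 − *d*) | Per group |
|---|---|---|
| 15% | 35.3 | 36 |
| 20% | 37.5 | 38 |
| 25% | 40.0 | 40 |

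The stated 38 is reproduced at 20%. The drop-out implied by 38 is 1 − 30/38 = 21.1%, inside the stated range. The plan's own figures therefore expect a sizeable group of leavers.

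**3. Expected leavers in the two exercise arms.** Only AT and RT bear on adherence to exercise. With 38 per arm, that is 2 × 38 = 76 people.

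- Per arm: 38 × 0.15 = 5.7 to 38 × 0.25 = 9.5.
- Both arms: 76 × 0.15 = 11.4 to 76 × 0.25 = 19.0, or about 11 to 19.
- If only 2 × 30 = 60 are allocated: 60 × 0.15 = 9 to 60 × 0.25 = 15.

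**4. How far that range can be trusted.** It assumes that the trial-wide rate applies equally to AT and RT and that every loss is someone who left the exercise programme. The Screening section allocates participants before the echocardiogram and stress ECG and excludes those who fail. The Intervention section adds four practice sessions before the intervention proper. People lost at those stages have little or no programme experience to report. If a share *f* of losses occurs after the programme proper begins, the relevant number is 11.4*f* to 19.0*f*. The documents do not give *f*; at an assumed *f* of one half, the range is 5.7 to 9.5.

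**5. Whether saturation repairs the gap.** Saturation means that further interviews bring no new themes from the kind of people being interviewed. It cannot reveal themes held only by people who are never approached.

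**The case against.** The strongest reply is that nothing in the article confines the interviews to completers. A reader might infer from the timing that leavers are excluded and that the adherence aim will be answered from finishers alone. The documents do not support that. They set no completion or attendance threshold, and the Qualitative study wording is attached to the individual, so an early leaver's last session is a possible reading. This stands, and it limits the point to the natural reading of the text.

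Second, a journal article may leave the choice of interviewees to the full protocol or to operating procedures, and Figures 1 to 3, which show the research plan and time points, are not visible here. This also stands as far as sampling rules go. However, the article itself states the time point three times, and the point concerns that time point.

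Third, non-adherence is wider than drop-out. Poor attenders who stay enrolled can be interviewed on any reading, and the attendance logs under Process evaluation could identify them. This stands: what is at risk is the account of why people stopped, not the whole adherence aim.

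Fourth, all nine pilot participants completed. That pilot ran 4 weeks against 12 in the trial and is too small to displace the plan's own 15–25%.

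Finally, fixed quotas of non-completers per arm and separate saturation for completers and non-completers are matters of preference. Their absence is not a fault.

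**Conclusion.** The point holds in a limited form. As timed, the interviews tend to miss exercise-arm participants who stop early, which sits badly with a component motivated by non-adherence. The number affected is roughly 11 to 19 of 76, on the assumption of equal drop-out in AT and RT with all losses from the exercise programme itself. It is lower to the extent that losses occur at the stress test after allocation or in the practice period. The consequence is under-representation of discontinuation in the themes, not loss of all information on non-adherence. The primary comparison of HbA1c is not touched.

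**What to change.** In the Qualitative study section:

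- hold the interview after the last scheduled session or at withdrawal, whichever comes first;
- invite all AT and RT participants who withdraw, by telephone if they cannot attend;
- include them among those on whom saturation is judged;
- report how many were approached and how many declined.

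Bring the timing statements in the abstract and the Study design section into line. If inclusion of leavers was always intended, the same wording settles it.

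The cost is small: the same interviewers and question guide serve, with a few off-schedule interviews. Some leavers will decline, so the gap may not close fully, but the reported counts will show its size.

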### Data and statistical analysis

Quantitative data will be processed and analyzed using SPSS version 20. To measure pre- and post-intervention absolute changes in glycaemia, anthropometry, body composition, metabolic and fitness parameters, liking/wanting for food and quality of life across the groups; a linear mixed model analysis for repeated measures that includes the covariates age and sex will be used. The SF-36 will be scored according to the guidelines provided by the RAND Corporation [40] and additionally effect size (Cohen’s d) will be assessed to determine change effect of each scale. The LFPQ will use Visual Analogue Scale (VAS) scores for explicit liking/ wanting for food and standardized ‘d-score’ (D-RT) for implicit wanting for food using E-prime software. The effect *p* = 0.05 will be considered statistically significant.

Qualitative data of the interviews will be audio recorded and verbatim transcribed for analysis. The facilitator and two observers will analyze their respective IDI using their notes (verbal and non-verbal responses of participants) and the tape-recorded data collectively immediately or within 24 h after the conclusion of the IDI. Transcripts will then be downloaded, coded, and analyzed for emergent themes using NVivo 10 qualitative analysis software [41]. The differences in coding will be resolved via discussions by a group of independent reviewers.

The data will be stored for future use after the completion of the study.

## Discussion

Findings from the proposed study are expected to benefit the knowledge base of health professionals in the South Asian region and provide further evidence for the development of specialised clinical exercise physiology services in the country.

Despite the high prevalence of T2DM in Sri Lanka, there are no published data on the effects of exercise in patients with the condition. Further, no adequately powered methodologically advanced trials have been conducted in South Asia to quantify multiple parameters regarding different modes of exercise prescription for patients with diabetes.

Differences in the body composition and metabolic profile of South Asians may differentially influence the relative effects of aerobic and resistance exercises, compared to other ethnicities. Further, the effects of exercise on food preference has not been investigated among South Asians and results will likely allow for better planning of lifestyle interventions for Sri Lankans.

Globally, the management of chronic non-communicable diseases (NCDs) is changing from a ‘disease’ to a ‘health’ model with a greater focus on lifestyle modification. This study is planned in a society where recreational ‘exercise culture’ is not a norm and the development of the new processes and services will be challenging. Findings of the proposed study will inform the development of a much needed professionally driven specialized service in behavior change and lifestyle modification to combat the NCD epidemic in the region.

The addition of a qualitative study to assess the barriers and facilitators for adherence to the intervention is also novel. Finally, we plan to triangulate quantitative and qualitative outcomes and propose a culturally adaptable therapeutic physical activity intervention to Sri Lankan patients with T2DM and inform policy makers.

